## Outcome definitions

- Cancer diagnosis recorded in the Danish Cancer Registry

## Analysis plan

- If possible (depending on power), we will present results for subtypes of hematological and brain cancers, rather than overall types. As a rule of thumb, we will not publish results based on analyses of outcomes with less than 20 events.

**Table 2.** Cancer outcomes

|                                                        | ICD-7                                                                                                                                                                                                                                                                                                                                                                                                                                                                                       | ICD-10                                                                                                                                                                                                                                                                                                                                                                                                                                                                                                                                                                                                                                                                              | Notes                                                                                                                                                                                                                                                                                                                                                                                                                                                                                                                                                                                                                                                            |
|--------------------------------------------------------|---------------------------------------------------------------------------------------------------------------------------------------------------------------------------------------------------------------------------------------------------------------------------------------------------------------------------------------------------------------------------------------------------------------------------------------------------------------------------------------------|-------------------------------------------------------------------------------------------------------------------------------------------------------------------------------------------------------------------------------------------------------------------------------------------------------------------------------------------------------------------------------------------------------------------------------------------------------------------------------------------------------------------------------------------------------------------------------------------------------------------------------------------------------------------------------------|------------------------------------------------------------------------------------------------------------------------------------------------------------------------------------------------------------------------------------------------------------------------------------------------------------------------------------------------------------------------------------------------------------------------------------------------------------------------------------------------------------------------------------------------------------------------------------------------------------------------------------------------------------------|
| Any cancer (excluding non-melanoma skin cancer) | "140" "141" "142"
"143" "144" "145"
"146" "147" "148"
"149" "150" "151"
"152" "153" "154"
"155" "156" "157"
"158" "159" "160"
"161" "162" "163"
"164" "165" "166"
"167" "168" "169"
"170" "171" "172"
"173" "174" "175"
"176" "177" "178"
"179" "180" "181"
"182" "183" "184"
"185" "186" "187"
"188" "189" "190"
"192" "193" "194"
"195" "196" "197"
"198" "199" "200"
"201" "202" "203"
"27559" "204" "205"
"206" "207" | "DC00" "DC01"
"DC02" "DC03"
"DC04" "DC05"
"DC06" "DC07"
"DC08" "DC09"
"DC10" "DC11"
"DC12" "DC13"
"DC14" "DC15"
"DC16" "DC17"
"DC18" "DC19"
"DC20" "DC21"
"DC22" "DC23"
"DC24" "DC25"
"DC26" "DC27"
"DC28" "DC29"
"DC30" "DC31"
"DC32" "DC33"
"DC34" "DC35"
"DC36" "DC37"
"DC38" "DC39"
"DC40" "DC41"
"DC42" "DC43"
"DC45" "DC46"
"DC47" "DC48"
"DC49" "DC50"
"DC51" "DC52"
"DC53" "DC54"
"DC55" "DC56"
"DC57" "DC58"
"DC59" "DC60"
"DC61" "DC62"
"DC63" "DC64"
"DC65" "DC66"
"DC67" "DC68"
"DC69" "DC70"
"DC71" "DC72"
"DC73" "DC74"
"DC75" "DC76"
"DC77" "DC78" | 
For exclusions of persons with previous cancer, we will exclude those with any cancer code except except non-melanoma skin cancer (have already been excluded from the list). However, in analyses of melanoma and keratinocyte skin cancer specifically, we will exclude those with previous history of non-melanoma skin cancer (ICD-7: 191; ICD-10: C44) as well.
 
Furthermore, in order to explore the impact of potential ascertainment bias of skin cancers, we will conduct a sensitivity analysis by repeating the all-cancer analysis after excluding all skin cancer (non-melanoma and melanoma skin cancer) from the outcome definition.
 |

## Analysis plan

|                       |       |                                                                                                                                                                                                                                      |                                                                                                                |
|-----------------------|-------|--------------------------------------------------------------------------------------------------------------------------------------------------------------------------------------------------------------------------------------|----------------------------------------------------------------------------------------------------------------|
|                       |       | "DC79" "DC80"
"DC81" "DC82"
"DC83" "DC84"
"DC85" "DC88"
"DC90" "DC96"
"DC91" "DC92"
"DC93" "DC94"
"DC95" except codes
for cutaneous
lymphoma ("C826"
"C840" "C841" "C848"
"C863" "C866"
"C884B") |                                                                                                                |
| Lung           |       | "C34"                                                                                                                                                                                                                                |                                                                                                                |
| Breast         |       | "C50"                                                                                                                                                                                                                                |                                                                                                                |
| Prostate       |       | "C61"                                                                                                                                                                                                                                |                                                                                                                |
| Pancreatic     |       | "C25"                                                                                                                                                                                                                                |                                                                                                                |
| Skin           |       |                                                                                                                                                                                                                                      |                                                                                                                |
| Melanoma              | "190" | "C43"                                                                                                                                                                                                                                |                                                                                                                |
| Keratinocyte cancers  | "191" | "C44" if any of the
following morphology
codes: "80903"
"80913" "80923"
"80933" "80973"
"81233" "80513"
"80523" "80703"
"80713" "80723"
"80733" "80743"
"80753" "80763"
"80943" "80953"                | Morphology codes will be used to identify BCC and SCC specifically (to exclude rarer NMSCs).                   |
| Haematological |       | All codes below                                                                                                                                                                                                                      | We will also compute estimates for overall hematological cancer and present if there is not power for subtypes |
| Lymphoma              |       | "C81" "C82" "C83"
"C84" "C85" "C86"
"C88" except codes
for cutaneous
lymphoma ("C826"
"C840" "C841" "C848"
"C863" "C866"
"C884B")                                                                               | We will make no distinction between Hodgkin's and non-Hodgkin's lymphoma (but will stratify if power allows)   |
| Multiple myeloma      |       | "C90"                                                                                                                                                                                                                                |                                                                                                                |
| Leukaemia             |       | "C91" "C92" "C93"
"C94" "C95"                                                                                                                                                                                                     |                                                                                                                |

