## Analysis plan

### *Eczema exposed*

- Persons with a diagnosis of atopic eczema (ICD-8: 691; ICD-10: DL20) in the Danish National Patient Registry between 1 Jan 1977 and 10 February 2018.
- We include all primary and secondary diagnoses for eczema from admissions, hospital outpatient clinics and emergency rooms in the Danish National Patient Registry, including ongoing contacts (that is, persons who at the end of study period are in active follow-up in a hospital outpatient clinic).
- Index date = The earliest hospital record for atopic eczema (date of admission or first outpatient appointment).
- Only persons who are born in Denmark and living in Denmark on the index date (i.e. date of first record for eczema).

For the current study, we will further restrict the study population as follows:

- We will exclude eczema patients (together with their matched comparators) identified by an ICD-8 diagnosis recorded together with an additional (“modification”) code indicating that it potentially an uncertain/unverified/working diagnosis (c\_diagmod=1–7).
- We will exclude patients (together with their matched comparators) with inconsistencies in registration of status and residence in the Civil Registration System (recorded as alive but not living in Denmark but without an emigration date), as we assume that these patients are not living in Denmark and thus not eligible.
- To ensure that we have at least 1 year of registration history from included registries (except the prescription registry), we will only include patients (together with their matched comparators) with index date on 1 January 1982 or later. In the subanalysis on severity and in a sensitivity analysis, we restrict to those diagnosed on 1 January 1996 or later in order to ensure one year of registration history in all databases.
- To ensure at least 1 year of follow-up after start of eligible follow-up (available until 30 June 2017), we will include eczema patients until 30 June 2016.
- We will exclude eczema patients (together with their matched comparators) with a record for any cancer (except non-melanoma skin cancer) before or on index date (see Table 2). That is, we will not only exclude those with history of the cancer outcome of interest. However, in analyses of non-melanoma skin cancer specifically, we will exclude those with previous history of this cancer as well.

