### *Unexposed cohort*

- Up to 10 persons matched to each eczema patient by sex and birth year.
- Comparators have to: (1) be born in Denmark, (2) be alive and living in Denmark on the on index date of their matched eczema-exposed individual (i.e. first hospital eczema diagnosis), and (3) have no previous diagnosis of eczema.
- Index date = The same index date as their matched eczema-exposed individual

As with eczema patients, we will additionally apply the following restrictions:

- We will exclude matched comparators with inconsistencies in registration of status and residence in the Civil Registration System (recorded as alive but not living in Denmark but without an emigration date), as we assume that these patients are not living in Denmark and thus not eligible.
- We will exclude comparators with any cancer (except non-melanoma skin cancer) before or on index date (see Table 2). That is, we will not only exclude those with history of the cancer outcome of interest. However, in analyses of non-melanoma skin cancer specifically, we will exclude those with previous history of this cancer as well.

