## Analysis plan

|                                                                               |  |                 |                                                                                                      |
|-------------------------------------------------------------------------------|--|-----------------|------------------------------------------------------------------------------------------------------|
| CNS                                                                    |  | All codes below | We will also compute estimates for overall CNS cancer and present if there is not power for subtypes |
| Meningioma                                                                    |  | “C70”           |                                                                                                      |
| Cancer of the brain, hypophysis, corpus pineale and ductus craniopharyngealis |  | “C71”           | If power is sufficient, we will look at glioma separately.                                           |
| Spinal cord, cranial nerve or other CNS tumours                               |  | “C72”           |                                                                                                      |

CNS: central nervous system

Note: All subcodes are included unless otherwise stated

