|                                                                                                    |                  | "DC94" "DC95"
"DC81" "DC82"
"DC83" "DC84"
"DC85" "DC86"
"DC88" "DC96"           |                                        |
| Use of oral corticosteroids                                                                        |                  | "H02AB" and
DOSFOR M "TAB"
or
"TABMO D"                                            | Any prescription excluding injections. |
| Systemic treatment for eczema (cyclosporine, azathioprine, mycophenolate, methotrexate, dupilumab) | Procedure codes: | "L04AX0 1"
"BOHJ18 B8"
"BWHB83 3"
"BWAH1 15"
"BOHJ20"
"BOHJ22"
"D11AH0 5" |                                        |
| Asthma                                                                                             | "493"            | "DJ45" "DJ46"                                                                               |                                        |

Note: All subcodes are included unless otherwise stated; all types of contacts (inpatient, outpatient and emergency) and both primary and secondary diagnoses should be considered. Use admission/prescription/record date for all variables.

aBaseline information only

bDocumentation is available here:

<https://www.dst.dk/da/Statistik/dokumentation/Times/forskningsservice/efalle>

<https://www.dst.dk/da/Statistik/dokumentation/Times/cpr-oplysninger/c-faelle-id>

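### The 'Any cancer' ICD-10 list leaves out DC86, so C86 lymphomas other than C863 and C866 count as lymphoma but not as any cancer, and the list disagrees with the prior-cancer exclusion that relies on it

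*Protocol*

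**What the plan says.** In Table 2 (Cancer outcomes), the ICD-10 column for 'Any cancer (excluding non-melanoma skin cancer)' lists DC81 to DC85 and then continues "DC85' 'DC88' 'DC90' 'DC96", followed by DC91 to DC95. The row closes with an exception for seven cutaneous lymphoma codes: "DC95' except codes for cutaneous lymphoma ('C826' 'C840' 'C841' 'C848' 'C863' 'C866' 'C884B".

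The Lymphoma row carries the same exception but a different parent list: "C84' 'C85' 'C86' 'C88' except codes for cutaneous lymphoma". A footnote to the table sets the reach of each parent code: "Note: All subcodes are included unless otherwise stated".

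The entry criteria use this table. Eczema patients are removed "with a record for any cancer (except non-melanoma skin cancer) before or on index date (see Table 2". The Unexposed cohort section repeats the rule: "We will exclude comparators with any cancer (except non-melanoma skin cancer) before or on index date (see Table 2". The note beside the 'Any cancer' row links that exclusion to the row's own codes: "we will exclude those with any cancer code except except non-melanoma skin cancer (have already been excluded from the list". The same note identifies non-melanoma skin cancer as ICD-7 191 and ICD-10 C44.

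In Table 3, the immunosuppression code list includes "DC85' 'DC86' 'DC88' 'DC96" among its haematological codes. The Follow-up section ends follow-up at a person's first cancer diagnosis and gives no separate code list for that rule.

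**The concern.** Two things do not fit together. First, a code that counts in a specific cancer row should also count in 'Any cancer', apart from the intended omission of non-melanoma skin cancer. C86 does not. Risk of all cancers leads the primary aim, so the gap is in the code list of the leading outcome, and the analysis that repeats it without skin cancers (item 16) inherits it.

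Second, one list does two jobs that need different content. Keeping cutaneous lymphoma out of the outcome is a reasonable choice. When the same list screens for earlier cancer, the exception lets in people whom the text says are excluded. What is at stake is whether the cohort that is built matches the cohort that is described, with lymphoma as the outcome most directly concerned.

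**Working it through.** The plan states no figure on this point and no sample-size or error-rate arithmetic applies. The check compares code lists, all taken from Tables 2 and 3.

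1. **'Any cancer' against the full range C00 to C97.** Absent categories: C44, C86, C87, C89 and C97. C44 is intended. C87, C89 and C97 are used by no outcome row in Table 2, so they create no conflict within the table. That leaves C86.

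2. **Each specific cancer row against 'Any cancer'.** Lung, breast, prostate, pancreatic, melanoma, multiple myeloma, leukaemia, meningioma, brain, and spinal cord/other CNS: no code falls outside. Keratinocyte: C44 falls outside, as intended. Lymphoma: C86 falls outside. The overall haematological row takes in all the codes below it, so it contains C86 too.

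3. **The exceptions against their parent codes.** Of the seven excepted codes (C826, C840, C841, C848, C863, C866, C884B), C863 and C866 have no parent in the 'Any cancer' row. All seven have a parent in the Lymphoma row. An exception with nothing to act on suggests that DC86 was meant to be listed.

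4. **Which lymphomas are mismatched.** Under the subcode footnote, C86 in the Lymphoma row brings in every C86 subcode except C863 and C866. Those remaining subcodes are lymphoma events and not 'Any cancer' events. C863 and C866 are outside both rows, so they add nothing to this mismatch.

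5. **The entry exclusion, text beside list.**
   - Text: every earlier cancer excludes, except 191/C44.
   - List, ICD-10: an earlier C86 code, or any of the seven cutaneous codes, does not exclude. The rest of C81 to C85 and C88 does.
   - List, ICD-7: 200 to 207 are all present with no cutaneous exception, and only 191 is missing between 140 and 207. The conflict is therefore on the ICD-10 side alone.

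6. **End of follow-up.** If the first-cancer rule is programmed from the same row, a first C86 or cutaneous lymphoma would not stop follow-up in the any-cancer analysis, and a later, different cancer could be taken as the first.

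7. **After adding DC86.** Every Lymphoma code lies inside 'Any cancer', both orphaned exceptions gain a parent, and C44 is the only specific-cancer code left outside. The seven cutaneous codes would still be missing from the entry screen, so the exclusion needs its own sentence.

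**The case against.** The strongest reply is that the prose already gives the right rule. The entry criteria exclude any earlier cancer other than non-melanoma skin cancer, and a programmer who followed the text would exclude prior C86 and cutaneous lymphoma. This stands in part: the plan contains no decision to admit these people. But the criteria point to Table 2, and the note there says that the exempt codes have already been taken off the list. A programmer who followed the list would do something else, so text and list have to be reconciled.

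A second reply is that the cutaneous exception is deliberate. That is correct for the outcome: it is explicit and identical in both rows, and it is not criticised here. Only its carry-over to the entry screen is.

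A reader might also infer more than the protocol supports:

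- *That people with earlier lymphoma in general enter the cohort.* They do not. The gap covers only ICD-10 C86 and the seven cutaneous codes.
- *That earlier C86 disease will be counted as new lymphoma.* This would need a further countable record after the index date. It also depends on how the first-cancer rule is coded: if it looks back over all cancer codes, such a record is not a first cancer.
- *That the lymphoma hazard ratio is inflated by some percentage*, because cutaneous lymphoma labelled as eczema gathers among the exposed and is later recoded. Such a figure would need the prevalence of these diagnoses in each cohort, the chance of a later countable code and a baseline lymphoma risk. The protocol gives none of these and describes no such recoding.

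**Conclusion.** The point holds as an inconsistency in an operative code list. The omission of DC86 from 'Any cancer' is clear from the table itself and rests on no assumption. Its direct effect is that C86 lymphomas other than C863 and C866 enter the lymphoma and haematological results but not the all-cancer result.

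The entry-exclusion point holds in a limited form: on the ICD-10 side the list is narrower than the rule it is meant to implement. Whether anyone is wrongly admitted depends on whether the programmer follows the text or the list.

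The number affected is probably small and cannot be computed from the document. No bias in any hazard ratio is claimed. The correction is worth making because it is nearly free and concerns the leading outcome, not because the results are expected to move much.

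**What to change.** 1. Add DC86 to the ICD-10 list for 'Any cancer' in Table 2 (Cancer outcomes), and keep the seven cutaneous lymphoma exceptions for the outcome.

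2. Add a sentence to the note in that row saying that these exceptions apply to the outcome only. The prior-cancer exclusion in both cohorts, and the first-cancer rule in the Follow-up section, should then cover DC86 and the cutaneous lymphoma codes, as the text already implies.

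The cost is two edits and no new data. A few people will leave the cohort. A comparator is removed alone, while an eczema patient is removed together with up to 10 matched comparators, so at most 1 + 10 = 11 persons are lost per exposed case.
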